#### Missing data

Variables with missing values in a small proportion of participants will be imputed using multiple imputation methods. To assess the missing at random assumption, we will evaluate the comparability between samples with missing data and those without. Sensitivity analysis will be performed by comparing the results obtained from the complete data analysis to the results obtained from multiple imputation.

### Model building

We have previously identified key biomarkers using a machine learning approach [10, 28–30]. We have further refined this analysis pipeline and will utilize this methodology to identify AHR, GERD, AHR/GERD overlap, and BE biomarkers**.** Specifically, we will utilize random forests (RF) of the filtered, normalized biomarkers. Models assessed via a modified hamming distance between variable importance rankings of models with identical hyper-parameters. A refined profile of the top 5% of important biomarkers by MDA will be included in a gradient-boosted tree model (xgboost package, R-Project) to build a classifier of AHR, GERD, AHR/GERD overlap, and BE. A random hyperparameter space search determined a final model that maximized AUC_ROC_.

We will also use linear mixed-effects models will be used to assess the temporal trend of biomarkers with time adjusting for confounders. The longitudinal biomarkers processes will be associated to risk of developing WTC-GERD/BE using the joint modeling technique [101]. The joint-modeling approach has become the primary method for analysis of longitudinal biomarker process and time-to-event outcome, and multiple R packages are available to implement the models. We will also consider a single index longitudinal model which enables us to reduce the dimensionality of multiple biomarkers and to evaluate joint effects of multiple biomarkers together to identify key risk factors. The single-index model incorporates longitudinal data to calculate hazard of each parameter as well as personalized dynamic risk for prognostication. Specifically, this will allow us to use a patient’s data from a single clinical exam to identify risk of GERD, AHR, overlap, or BE. Furthermore, this will allow the identification of false negatives and undertreated cases in the entire FDNY cohort.

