### Power analysis

A sample size of 40 cases for each group of GERD, AHR, AHR/GERD overlap, BE, and non-GERD/non-AHR Controls (all will be subsets of AIM 1 *N =* 898 randomly selected cohort) achieves 80% power to detect difference as small as 0.78 SD with two-sample t-test at 0.01 significance level to account for multiple comparisons. This will allow us to achieve 80% power and significance of 0.05, based on prior studies with salivary pepsin test (personal communication with [name] of Peptest), Fig. 2.

*Statistical Analysis* SPSS 28 (IBM) will facilitate database management and statistics. Continuous variables expressed as mean, standard deviation (SD) if normally distributed, and as median, inter-quartile range (IQR) if skewed. Two-sample t-test and ANOVA will compare continuous data. Count and proportions will summarize categorical data and Pearson- χ^2^ will compare categorical data. Multivariate binary logistic regression will estimate biomarker-disease relationship for case status as a binary outcome while adjusting for confounding. Cox proportional hazards model will evaluate the effects of biomarkers, smoking, and exposure on the hazard of developing WTC-GERD or BE over time. The maximum potential effectiveness of a biomarker will be calculated by Youden Index [100]. Goodness of fit, using the Hosmer–Lemeshow test. Survival curves compared by Log-rank test. Pearson χ^2^-test will compare SABA and LABA usage between GERD, AHR, AHR/GERD overlap, BE, and non-GERD or AHR controls. Significance will be assessed by *p <* 0.05 for all statistical tests. Graphs will be created using Prism (v.10, GraphPad Software).

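### The stated biomarker selection is a fixed top-5% quota with no null reference, so it always returns a list and does not separate true markers from the noise that fills it

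*Protocol article*

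**What the plan says.** All of this is in the Protocol article. Under Model building, the authors "will utilize this methodology to identify AHR, GERD, AHR/GERD overlap, and BE biomarkers". The steps given there are:

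- Ranking: "we will utilize random forests (RF) of the filtered, normalized biomarkers". The filter, the number of markers and the number of trees are not given.
- Check: "Models assessed via a modified hamming distance between variable importance rankings of models with identical hyper-parameters". No cut-off is given, and the text does not say whether the compared models share the same participants.
- Selection: "A refined profile of the top 5% of important biomarkers by MDA will be included in a gradient-boosted tree model".
- Final classifier: "A random hyperparameter space search determined a final model that maximized" the area under the ROC curve.

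The Power analysis section gives the group size ("A sample size of 40 cases for each group") and the only design calculation ("achieves 80% power to detect difference as small as 0.78 SD with two-sample t-test at 0.01 significance level"). The statistical analysis paragraph there also plans t-tests, ANOVA and confounder-adjusted logistic regression, judged at "0.05 for all statistical tests". Model building does not make any of these a condition for a marker to enter the list.

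**The concern.** A rule said to identify biomarkers should be able to say that a marker, or the whole panel, is not one. A fixed share cannot, because its length depends only on panel size. A stability check could guard against this if it tested whether the ranking recurs in other people. Agreement between forests rerun on the same people with the same settings tests only whether enough trees were grown, since chance associations in one data set are ranked reproducibly too.

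This matters here for two reasons. The section on limitations accepts that there may be no association to find. The Discussion hopes that validated serum proteins and metabolites will offer a plausible target for detection and therapy. Metabolome, microbiome and protein panels set against 40 participants per group leave much room for chance rankings.

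**Working it through.** **1. The plan's own figure.** Inputs from Power analysis: n = 40 per group, difference d = 0.78 SD, alpha = 0.01, taken as two-sided. Normal approximation: power = Φ(d√(n/2) − z₀.₉₉₅) = Φ(0.78 × 4.472 − 2.576) = Φ(0.912) = 0.819. The exact noncentral t gives 0.799. So the stated 80% reproduces. It describes one marker tested by one t-test and says nothing about the forest selection.

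**2. The quota.** Number listed = 0.05p, that is 5 of 100, 25 of 500 or 50 of 1,000. If m markers are truly associated, at least 0.05p − m of those listed are false. With p = 500 and m = 5, at least 20 of 25 are false; with m = 0, all 25 are. Requiring MDA above zero would not help: in every pure-noise run, every listed marker had MDA above zero.

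**3. Rank agreement on the same participants.** Assumptions, because the article gives no figures: 40 vs 40, independent standard normal markers, p = 100 or 500, √p features per split, out-of-bag permutation MDA, and two forests per data set differing only in seed. Measure: share of the top 5% common to both lists. Chance for p = 500 is 25 × 25/500 = 1.25 markers, or 5%.

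| Setting | Trees | Mean overlap |
|---|---|---|
| Noise, p = 500 (8 data sets) | 500 | 37% |
| | 2,000 | 62.5% |
| | 6,000 | 79% (range 68-88%) |
| Noise, p = 500 (2 data sets) | 20,000 | 86% |
| | 40,000 | 84% |
| Five true 0.78 SD markers, p = 500 (3 data sets) | 6,000 | 80%, 84%, 84% |
| Noise, p = 100 (8 data sets) | 500 | 55% |
| | 2,000 | 77.5% |
| | 6,000 | 87.5% |

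At 6,000 trees the three signal values lie inside the noise range. In those signal runs 4 to 5 of the 5 true markers were in the top 25, so the ranking works; the check does not tell the two situations apart. Rank correlation over the whole noise list also rose with trees: 0.10, 0.26 and 0.41 at 500, 2,000 and 6,000 (p = 500). A separately coded simulation (p = 200, 8,000 trees, six data sets each) gave a mean overlap of 90% for noise and 90% with five true markers.

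**4. Agreement across different participants.** With p = 500 noise markers, lists from different data sets overlapped by 0-5%. Lists from disjoint halves of one data set overlapped by 4-8%. Both are close to the 5% expected by chance, so a check across participants would expose a noise list.

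**5. How many permutations a null reference needs.** With B permutations, the smallest p-value for one marker is 1/(B + 1). The Benjamini-Hochberg threshold for a single discovery among 500 markers at 5% FDR is 0.05/500 = 0.0001, which needs B ≥ 9,999. With B = 1,000 the floor is 1/1,001 ≈ 0.001, so at least 10 markers would have to reach it together (10 × 0.0001 = 0.001). Pooling the null across markers gives 1,000 × 500 = 500,000 null values and removes that floor.

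**The case against.** The best case for the plan has four parts.

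*The top 5% is feature reduction, not a declaration.* The sentence feeds those markers to a boosted-tree classifier, and a fixed fraction is a permissible choice for that. This stands for the classifier. It does not cover the stated aim of identifying biomarkers, for which no other rule is given.

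*The compared models may not share participants.* They could be fitted to resamples or folds, and the check would then carry information on association. The text does not exclude this, so the criticism of the check is conditional. The criticism of the quota is not.

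*The simulations rest on chosen inputs.* Panel size, tree count and the 40 vs 40 contrast are assumed, the data sets are few, and top-5% overlap is not the modified Hamming distance, which the article does not define. A reader might infer that pure noise always yields a stable list; at 500 trees and 500 markers it does not (37%). The result holds with enough trees, and a stability criterion itself favours more trees.

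*The study can still report null results.* The t-tests, ANOVA and logistic regression can do so. An AUC from data not used for selection would show an all-noise list to be useless (0.50 on new data in the simulation), though it would not sort true markers from false ones in a mixed list. So it would be wrong to infer that the study as a whole cannot show the absence of association.

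Nor does the point rest on missing validation detail, which a fuller plan may hold.

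**Conclusion.** The point holds for the stated selection rule and should be corrected. As written, the rule returns 5% of the panel with certainty and attaches no error rate to it. If five of 500 markers were real, at least 20 of the 25 listed would be false. That part is arithmetic and needs no assumption about the forest.

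The rank-agreement check does not repair this if the models are reruns on the same participants. Noise lists then agree almost as well as lists with signal (79% against 80-84% at 6,000 trees), subject to the assumed panel size and tree count.

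A stronger reading, that the selection has nothing to do with association, is not supported: MDA is computed against case status and ranks true markers high. What is missing is a line between those markers and the rest of the quota.

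**What to change.** Keep the top 5% as input to the boosted-tree classifier if wished, but separate it from the claim of identification.

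- Call a marker identified only if its MDA exceeds a null distribution obtained by permuting case status and refitting the forest, at 5% FDR. State that the list may be empty.
- Pool the null across markers, or run enough permutations to resolve the threshold (step 5 of the working). Pooling assumes that markers share a similar null distribution of MDA; pooling within assay platform is a reasonable compromise.
- Do not permute within confounder strata: at 40 per group the strata become thin. Leave confounding to the adjusted logistic regression already planned.
- Assess rank stability over bootstrap or subsample draws of participants, and say so. If that is already the method, one sentence settles it.

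The cost is computing time and a paragraph of text. Recruitment, visits and assays do not change. The downside is a list that may be shorter than 5% of the panel, or empty.

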## Methods/design

### Study design and participants

The FDNY WTC-health program (WTC-HP) electronic medical record (EMR) will be used to obtain clinical variables such as age, gender, years of FDNY service, WTC site exposure level, and lung function measures, as previously described [22, 27, 62–65, 71]. Our observational study is NYU IRB Approved # 21–00679 and available at clinicaltrials.gov #NCT05216133. Study Definitions and Inclusion/Exclusion Criteria can be found in Table 1.

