*FeNO*, a biomarker of lung disease activity, will be a valuable measure in our population. FeNO is associated with airway hyperreactivity, and several studies demonstrated that FeNO is increased during obstructive exacerbations [120]. In our population with the aerodigestive overlap, FeNO levels can serve as an indicator of potential underlying AHR exacerbating symptoms of GERD. Thus, our work will also contribute to understand the role of FeNO in GERD, which remains inconclusive as only a limited number of studies have examined AHR/GERD [121, 122]. The detrimental impact of even once-weekly episodes of GERD on quality of life [123] highlighted the importance of assessing aerodigestive disease quality of life and disease activity, therefore we will quantify the effects of GERD on these aspects through a validated set of questionnaires that will assess QoL, GERD specific symptoms and also cognitive involvement.

Non-invasive biomarkers of GERD, BE, AHR, treatment efficacy, and severity of symptoms will also be assessed in serum. This will allow us to measure Tumor Necrosis Factor (TNF-α), C-peptide, Fractalkine and Interferon-gamma-induced Protein 10 (IP-10) in our case cohort study to validate our prior pilot study [1–3]. Serum samples will also be used to perform metabolomic profiling that will allow us to investigate metabolic correlates of aerodigestive disease. In addition, by validating serum biomarkers (proteins and metabolome) of GERD/BE, we seek to provide a biologically plausible target that enables early detection and facilitates therapeutic intervention in the PM exposed populations. Moreover, non-invasive phenotyping of WTC aerodigestive disease holds promise in improving the sensitivity and specificity of GERD diagnosis, enabling earlier identification of BE and facilitate the development of personalized therapy, thus to improve both the quality of life and overall health outcomes.

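### The classifier is described as biomarker-only and chosen by maximum AUC with no clinical comparator, so its AUC alone cannot show that the biomarkers add to noninvasive information the study already collects

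*Protocol article*

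**What the plan says.** The Model building section sets out the classifier from inputs to selection rule.

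- Inputs to the ranking step: "we will utilize random forests (RF) of the filtered, normalized biomarkers".
- Inputs to the classifier: the top 5% of biomarkers by importance, which "will be included in a gradient-boosted tree model (xgboost package, R-Project) to build a classifier of AHR, GERD, AHR/GERD overlap, and BE".
- Choice of the final model: "A random hyperparameter space search determined a final model that maximized" the AUC.

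No clinical covariate and no reference model is named at any of these steps.

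Clinical information on the same men is planned elsewhere in the article. Study design and participants lists "clinical variables such as age, gender, years of FDNY service, WTC site exposure level, and lung function measures" from the medical record. The measurement visit adds spirometry with percent predicted values, PAGI-SYM and SGRQ. Smoking is a term in the planned Cox model.

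Confounding is addressed in other models. Under Statistical Analysis, the logistic regression is adjusted and the Cox model includes smoking and exposure. Under Model building, the linear mixed models are adjusted.

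On what the work may achieve, the Discussion (text under the heading Microbiome of the gut/lung axis) says that "non-invasive phenotyping of WTC aerodigestive disease holds promise in improving the sensitivity and specificity of GERD diagnosis".

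**The concern.** The second aim in the Background is to build a noninvasive model, and the classifier is the model that assigns men to disease groups. Its AUC is likely to be read as the measure of what the biomarkers can do.

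Serum proteins, lipids and metabolites may track age, smoking and similar factors. If the groups differ on these, a model given biomarkers only can separate the groups through them. The AUC does not reveal the source of the separation.

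The study also gathers cheaper noninvasive information from the same men: age, exposure, spirometry and symptom questionnaires. Without a model built on these, a biomarker AUC cannot show whether fasting blood, metabolomics, breath condensate and swabs add anything. Improvement in diagnosis is a comparison, and the section names nothing to compare with.

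**Working it through.** **The plan's own figure.** Power analysis gives "A sample size of 40 cases for each group of GERD, AHR, AHR/GERD overlap, BE, and non-GERD/non-AHR Controls" and states that this "achieves 80% power to detect difference as small as 0.78 SD with two-sample t-test at 0.01 significance level to account for multiple comparisons". A noncentral-t calculation with 40 v 40, a difference of 0.78 SD and two-sided alpha 0.01 gives power 0.799, so the figure reproduces. It concerns a difference in means on one measure. The article gives no sample-size figure for the classifier or its AUC.

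**AUC from clinical factors alone.** The article gives no group differences in age, smoking or similar factors, so the inputs here are assumptions. Suppose k independent, normally distributed factors each differ by d SD between two groups, and the panel captures them fully. Then D = d√k and AUC = Φ(D/√2), with no disease-specific signal.

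| d (SD) | k = 1 | k = 2 | k = 3 |
|---|---|---|---|
| 0.3 | Φ(0.212) = 0.58 | Φ(0.300) = 0.62 | Φ(0.367) = 0.64 |
| 0.5 | Φ(0.354) = 0.64 | Φ(0.500) = 0.69 | Φ(0.612) = 0.73 |

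**Incomplete capture.** Full capture is an upper bound. Now take 10 biomarkers, each correlated ρ with a single factor and linked to disease only through it. Then D² = 10ρ²d²/(1 + 9ρ²).

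- ρ = 0.3: 10(0.09)/(1 + 0.81) = 0.497, so D = 0.705d. AUC is 0.56 at d = 0.3 and 0.60 at d = 0.5.
- ρ = 0.5: 10(0.25)/(1 + 2.25) = 0.769, so D = 0.877d. AUC is 0.57 at d = 0.3 and 0.62 at d = 0.5.

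At d = 0.8 the two values are 0.66 and 0.69.

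**Can imbalance explain a high AUC?** For AUC 0.80, Φ⁻¹(0.80) = 0.842, so D = 0.842 × √2 = 1.19 and D² = 1.417. At d = 0.5 this needs k = 1.417/0.25 = 5.7, that is, six independent factors. At d = 0.3 it needs k = 1.417/0.09 = 15.7, that is, sixteen. Ordinary imbalance does not get there.

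**Precision at 40 v 40.** The Hanley–McNeil standard error at AUC 0.70 is 0.0585. The 95% CI is 0.70 ± 1.96 × 0.0585, about 0.59 to 0.81.

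**Precision of the AUC difference.** Take a reference AUC of 0.65 (SE 0.0614), a combined AUC of 0.75 (SE 0.0547) and a correlation r between the two estimates. The SE of the difference is √(0.0614² + 0.0547² − 2r × 0.0614 × 0.0547).

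| r | SE | 95% CI half-width | Power, two-sided 0.05 |
|---|---|---|---|
| 0.3 | 0.069 | 0.13 | 31% |
| 0.5 | 0.058 | 0.11 | 40% |
| 0.7 | 0.045 | 0.09 | 60% |

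The correlations are also assumed. The difference can be estimated, but only loosely.

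**The case against.** **This is a condensed article.** Tables 1 and 3 and Figures 1 and 2 are not shown, and classifier covariates or benchmark models may sit in a fuller plan. This stands as a caution. However, Model building is not merely silent: it states the inputs and the selection rule, and the comment is on that stated method.

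**The panel may be broader than laboratory markers.** The Background counts severity and quality-of-life scores among the noninvasive measures. The Discussion refers to Table 3 for its broad biomarker profile, and that table's legend lists FEV1, SGRQ and PAGI-SYM. This stands. It strengthens the case for separate models, because the AUC could then come from the questionnaires or spirometry.

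**Confounding is adjusted for elsewhere.** The adjusted logistic regression does address whether a biomarker carries information beyond confounders, and the Cox model includes smoking and exposure. This stands for association. None of these models gives the added discrimination of the classifier.

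**Stronger readings a reader might infer.**

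- That unmatched groups are a defect. The article describes no matching, but in a condensed text that is only silence. Matching is optional and would complicate estimating added value.
- That ordinary imbalance equals the effect the study is powered for, by converting 0.78 SD to an AUC. That effect belongs to a t-test on a single measure and is not a target for the classifier.

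**Conclusion.** The point holds in a limited form. As described, the classifier uses biomarkers only, is selected on AUC, and has no clinical comparator. A modest AUC of about 0.6 to 0.7 could reflect clinical factors. Across the cases with d of 0.3 to 0.5, the calculated range is 0.56 to 0.73. So the AUC alone cannot show that the biomarkers add to noninvasive information already collected.

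The size rests on assumed imbalances of 0.3 to 0.5 SD, on independence and normality of the factors, and on how well the panel captures them. It does not extend to a high AUC.

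A reader might go on to infer that the study could not support its conclusion. The article does not bear that out. The gain in diagnosis is worded as promise in the Discussion, the contrast drawn there is mainly with invasive testing, and the adjusted logistic regression partly answers whether the markers carry disease information. This is a worthwhile improvement to the method, not a fatal flaw.

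**What to change.** For each target, fit three models in the same resampling folds:

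- (a) a clinical reference model from variables already collected or planned: age, smoking, WTC exposure level and FEV1 % predicted, plus PAGI-SYM for GERD/BE and SGRQ for AHR;
- (b) the biomarker-only model, with questionnaires and spirometry kept out;
- (c) the combined model.

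Report all three AUCs and the difference (c) minus (a) with its confidence interval. Base any statement of improved diagnosis on that difference. Do not make it a pass/fail gate: with power of about 31% to 60% for a rise from 0.65 to 0.75, a rule that the interval must exclude zero would often discard real markers.

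The cost is a few more model fits on existing data, a headline gain that will probably look smaller than the biomarker-only AUC suggests, and a wide interval at 40 per group (roughly ±0.09 to ±0.13 in the example above).

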### Study population

#### Source cohort

All participants in the WTC-HP (*n =* 14,976) were screened, Fig. 2. *Inclusion Criteria:* i. Actively consented and enrolled member of the WTC-HP. ii. Pre-9/11 spirometry with Forced Expiratory Volume in 1 s (FEV_1_) ≥ Lower Limit of Normal (LLN) iii. Male Firefighter status on 9/11 with exposure at the WTC-site and entry into WTC-HP before the site closure on 7/24/2002. *Exclusion Criteria:* i. lung disease prior to 9/11 as defined by positive methacholine or bronchodilator test, or FEV_1_ < LLN. ii. Not part of initial cohort in data extraction from August 1, 2017 [72]. After all inclusion/exclusion criteria applied, the baseline cohort consists of *n =* 4,192. *Sub-cohort Development.* A representative cohort of 20% was randomly selected (*n =* 837; SPSS v. 28) from the above baseline cohort, Fig. 2.

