**Fig. 2 Fig2:**
[figure not shown]
Study design

*Recruited Cohort* will be developed to assess for noninvasive biomarkers. We will recruit a subset *N =* 40/group (*i.* AHR only *ii.* GERD only *iii.* BE *iv.* GERD/BE and AHR overlap or *v.* No GERD nor AHR) from the sub-cohort, Fig. 2. Recruitment strategies will include: i. Direct mailings; ii. Email (potential participants will be sent the same IRB-approved recruitment message to their personal emails using end-to-end encryption; iii. Study website will include recruitment messages providing general information on the study and answers to frequently-asked questions. No direct communications will be made with participants through the website, and no PHI will be used or available within the study website; iv. Telephone contact. A description of the study will be provided to potential participants and, upon their expression of interest, the investigator will perform an eligibility screening. In addition to meeting the inclusion criteria as outlined above, participants should: i. have available serum from their first post 9/11 WTC-HP ii. Not currently be receiving treatment for malignancy iii. Have no limitations to a minimal risk blood draw iv. Be willing and able to sign consent; and v. be able to attend a single-visit.

All co-investigators have received training from the principal investigator in how to obtain consent and answer questions that may arise during the consent process. The consent and letter have been written to comply with the requirement that they be written at a 5th grade reading level, evaluated by the Flesch–Kincaid readability test. In addition, subject will be asked to provide their understanding of what the study is about at the time of the consenting process. English is the primary language of all FDNY rescue workers, see Appendix.

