### Blood sampling

After at least an 8 h fast, serum and plasma will be obtained, aliquoted and banked. Each stored specimen will be assigned a unique code to ensure proper identification and linkage to the respective participant. Aliquots from the fresh samples will be assayed for complete blood count (with differential) and chemistry panel. These data are already available for the banked samples. For all samples, lipid profile, metabolomics, and protein biomarker profiling will be performed [10, 28–30, 76, 77].

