### Limitations and potential study concerns

We envision there are several limitations of our study. It is possible that no significant association exists between noninvasive biomarkers and aerodigestive diseases in the second decade after WTC exposure. The generalizability of our study could be impacted because the FDNY source cohort had no aerodigestive disease prior to 9/11 and had their serum samples banked within six months of 9/11, therefore making it less comparable to other cohorts. There may also be a subset of patients without history of GERD, but could still receive a clinical diagnosis of GERD based on questionnaires and/or elevated pepsin/biomarkers. For these patients, further follow-up with a gastroenterologist will be recommended. Additionally, we may use FeNO levels to identify the potential underlying AHR exacerbating symptoms associated with GERD. We will also account for the potential risk of loss to follow-up regarding the completion of the questionnaires and attendance of the in-person visit.

Further investigation into the overlap of GERD/BE and AHR is envisioned to provide valuable insights in distinguishing disease phenotypes, demonstrating that biomarkers can predict GERD and/or BE. This work will have clinical implications for the diagnosis and treatment of WTC associated disease, as well as for the management of other patients in the WTC monitoring programs, and for the general population as intense PM exposures are occurring more frequently, for example through wild fire related PM. Our research will contribute to the development of a robust biomarker set with optimal explanatory power when applied to diverse cohorts.

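### On the serum sampling described, the planned overall time trend for the newly run serum assays cannot be separated from storage age; longitudinal claims should rest on group-by-time contrasts

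*Protocol article*

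**What the plan says.** The relevant statements are spread over several sections of the protocol article.

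- **Model building:** "linear mixed-effects models will be used to assess the temporal trend of biomarkers with time adjusting for confounders". The confounders are not named. The next sentence links the longitudinal biomarker processes to the risk of WTC-GERD/BE by joint modelling.
- **Early sample** (Recruited Cohort paragraph, under Fig. 2): participants must "have available serum from their first post 9/11 WTC-HP". Limitations and potential study concerns adds that the source cohort "had their serum samples banked within six months of 9/11". Source cohort gives a later outer bound, "entry into WTC-HP before the site closure on 7/24/2002".
- **Late sample:** participants must "be able to attend a single-visit". Blood sampling describes the draw: "After at least an 8 h fast, serum and plasma will be obtained, aliquoted and banked".
- **Assays:** Blood sampling says that blood count and chemistry already exist for the banked samples, and then: "For all samples, lipid profile, metabolomics, and protein biomarker profiling will be performed". These three panels are therefore to be run on both sets of serum.

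No serum draw between the two is described. The limitations section treats the early banking as a matter of generalizability only.

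**The concern.** A trend over time needs measurements that differ in time and not systematically in something else. Here every early value would come from serum stored for two decades, and every late value from serum that is nearly fresh. If storage changes an analyte, the change appears in the time coefficient.

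At stake is the reading of the overall trend for serum analytes such as TNF-α, C-peptide, fractalkine and IP-10, which the Discussion says will be measured to validate the pilot study, and for lipids and metabolites. Followed as written, the analysis could report a storage effect as a biological course after exposure. Adjusting for confounders looks like a safeguard but cannot work when the confounder is a linear function of the exposure variable.

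**Working it through.** **The plan's own figure.** The only power statement is for a cross-sectional two-sample t-test with 40 per group, 0.78 SD and a 0.01 level. The noncentral t (two-sided) gives 79.9% power, so the stated 80% reproduces. It does not bear on the trend model, for which no power is stated.

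**Step 1: gap between draws.** Inputs: banking from 11 September 2001 to about 11 March 2002 (within six months of 9/11). Visit dates are not given, so I assume they lie between registration (31 January 2022) and publication (9 August 2024).

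- Shortest: 11 March 2002 to 31 January 2022 = 19.9 years (19.5 if the 24 July 2002 program-entry limit is used).
- Longest: 11 September 2001 to 9 August 2024 = 22.9 years.

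**Step 2: aliasing.** Storage age at assay = assay date − draw date.

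- *All samples assayed in one campaign:* the assay date is a constant c, so storage age = c − draw time. The correlation is exactly −1, and the design matrix [1, time, storage age] has rank 2 of 3. Both terms cannot be fitted.
- *Visit samples assayed within a year of the draw, banked samples in one campaign:* with 200 people and two draws each, the simulated correlation is −0.9987. The variance inflation factor is 1/(1 − r²), about 388. Assay run is then aliased with time as well.

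**Step 3: how small a shift matters (illustration only).** The document gives no storage effect, SD or within-person correlation; all are assumed here. Take no true change, a storage shift of b SD in either direction and within-person correlation ρ. The SD of the change is √(2(1 − ρ)), and the noncentrality is b·√n / √(2(1 − ρ)). With n = 5 × 40 = 200 and the stated 0.05 level (two-sided), the probability of a significant trend is:

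| Shift b | ρ = 0.3 | ρ = 0.5 | ρ = 0.7 |
|---|---|---|---|
| 0 | 5% | 5% | 5% |
| 0.1 SD | 22% | 29% | 44% |
| 0.2 SD | 66% | 80% | 95% |
| 0.3 SD | 95% | 99% | 100% |

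Example: b = 0.2, ρ = 0.5 gives 0.2 × √200 / 1 = 2.83, hence 80%.

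As a proportional loss, b = −ln(1 − loss)/SD on the log scale. With SD 0.5 and ρ = 0.5, a 5% loss is 0.103 SD (30%) and a 10% loss is 0.211 SD (84%). With SD 1.0, a 10% loss gives 32% and a 20% loss 88%.

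**Step 4: what is protected.** I considered five groups of 40, a common shift of 0.3 SD, ρ = 0.5, no true change and 4,000 simulated studies. The main effect of time was significant in 98%, and the group-by-time test in 5.0%. A shift common to all groups cancels from differences in change. It also cancels from any comparison within one sample era.

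**The case against.** **The sample set is inferred.** Model building does not say which samples enter the mixed model, and the cohort has other longitudinal data: clinical phenotyping, lung function, and blood count and chemistry already on file for the banked samples. This stands as a limit. The point covers only the newly run lipid, metabolome and protein assays, for which no other repeated source is described.

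**The overall trend is not an aim.** The three stated aims concern phenotyping, a biomarker model, and quality of life and cognition. The Outcomes paragraph lists no serum analyte. Disease contrasts are largely protected, and in a joint model with a current-value link and a flexible baseline hazard, a storage shift that depends only on time would be absorbed by that hazard. This largely stands and keeps the point modest. But the trend is a stated analysis, and serum analytes are among the planned readouts.

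**The size is assumed.** This is correct. Neither the size nor the direction of any storage effect is known, and the probabilities in step 3 restate the shift that was put in. The aliasing does not depend on them.

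**Laboratory detail belongs elsewhere.** Plate layout and sample handling are commonly left to a manual or analysis plan, and their absence from an article is no fault. However, no later choice of covariates can separate two aliased terms.

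**Two stronger readings are not supported.** A reader might infer that a cut-point set on banked serum will misclassify when applied to fresh serum, because the article says that "this will allow us to use a patient’s data from a single clinical exam to identify risk of GERD, AHR, overlap, or BE". No section says the classifier is trained on banked serum or that a threshold is carried across. A reader might also infer that fasting state differs between the samples. The article states the fast for the new draw and is silent on the banked serum, and silence is not evidence of a difference.

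**Conclusion.** The concern holds in a limited form. If the repeated measures for the newly run serum assays are the banked and the visit samples, as the sampling described implies, the main effect of time cannot be distinguished from a storage effect over about 20 to 23 years. The correlation between the two is −1, or about −0.999, and covariate adjustment does not help. This rests on the inferred sample set and on visits between registration and publication. Whether a storage effect exists, and how large it is, is unknown.

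Group differences in change and comparisons within one era remain valid if storage acts equally in all groups. FeNO, breath condensate and salivary pepsin are described only at the new visit and are not affected. The change is worth making because it is cheap and because the assay layout cannot be repaired once the samples have been run.

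**What to change.** In Model building:

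1. State which samples enter the mixed model. For the newly run serum assays, work on the log scale and base longitudinal claims on the group-by-time contrast, with the no-GERD/no-AHR group as reference. State that the main effect of time is not interpreted as a biological trend.
2. Assay each participant's banked and visit aliquots in the same run, with the five groups balanced across runs.
3. If values from both eras would enter one classifier, standardise each analyte within era or use visit serum only.

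The cost is wording and plate layout; no new participants or draws are needed. The downside is that the overall time trend is given up as a conclusion. The group-by-time contrast still assumes a proportional storage effect common to all groups, and the plan should say so.
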